**Fig. 1 Fig1:**
[figure not shown]
Design of the study. Cohort: prospective cohort; Group A, B, C: steps in the stepped-wedge based design. Q = quarter

### Intervention

NPRL2.0 is an integrated, transmural healthcare network for patients with CMP, focusing on improving the level of functioning of patients, despite pain. In the primary care of NPRL2.0, the GP is the gatekeeper for assessing the level of complexity of pain complaints, referral, and treatment selection. In the Netherlands, therapists (such as physiotherapists, practice therapists, and occupational therapists) in primary care can be visited by people with CMP directly, without referral. Therefore, therapists will also be able to assess the level of complexity of the pain complaints and to advise these patients to visit a GP if necessary. Depending on the level of complexity involved, the follow-up policy will either include advice without further treatment, monodisciplinary treatment in primary care, interdisciplinary treatment in primary care (collaboration between GPs, primary care therapists, and mental health practice nurses in assessing and treating patients with CMP who need mental support besides physical exercise) or interdisciplinary treatment in secondary or tertiary care (Fig. 2). Primary care in NPRL2.0 consists of the following elements:

**Fig. 2 Fig2:**
[figure not shown]
Referral options within Network Pain Rehabilitation Limburg: previously published in Lamper et al. [73]

#### Integral focus on assessment and referral: assessment tool

To support the healthcare professionals in their decision-making for problem-mapping and treatment selection, an evidence-based objective assessment tool will be used for the assessment of complexity of the pain problem: the STarT MSK Tool [35]. The Dutch version of this tool is translated and validated (not published yet). STarT MSK will support decision-making by choosing the right treatment to match the patient’s biopsychosocial profile.

#### Integral focus on treatment content and duration: treatment protocols

Patients will receive individualized treatments based on their current needs in order to improve their daily functioning. NPRL2.0 protocols are based on the most recent evidence-based treatment methods, such as Graded Activity, Exposure in vivo, and Acceptance and Commitment Therapy, and are adjusted to the primary care setting [22–24, 36, 37]. In the feasibility study, healthcare professionals were invited to provide feedback on the NPRL2.0 treatment protocols. Based on this, adjustments were made to the content and duration of NPRL2.0 treatment protocols. The primary care NPRL2.0 protocols are extended with a module focusing on self-management in daily living after treatment by a primary care therapist. In these treatment protocols, no advice for medication will be described. It is hypothesized that the biopsychosocial oriented healthcare professionals working in NPRL2.0 will prescribe less medication compared to patients receiving usual care.

#### Integral focus on self-management: eHealth application

Healthcare professionals and patients participating in the NPRL2.0 will make use of the eHealth application: SanaCoach Pain Rehabilitation [38]. The coach's primary goal is to support self-management. Its main function is to provide module-based pain education. Different eLearning modules are developed for the patients in order to teach them about the biopsychosocial aspects of pain. In addition, diaries are integrated in which patients can provide information on their pain intensity, level of activity, mood, and participation level. Moreover, healthcare professionals can use scores from these diaries to adjust treatment protocols to the needs of individual patients. The application also consists of a chat function between the patient and their healthcare professionals to ensure prompt communications. The functions in the SanaCoach Pain Rehabilitation, such as the number of diaries and the level of education, will be adapted to the patient, based on his/her complexity and level of disability.

#### Education and collaboration

Healthcare professionals will receive education during the 3-month wash-out period: GPs 2 × 3 h and therapists 3 × 3 h. Topics in the education program include biopsychosocial theories of CMP, recognition of patients with or at risk of CMP, providing education to patients with CMP, use of the assessment tool and eHealth application, and treatment selection. The first two sessions are organized jointly for all disciplines of healthcare professional in order to promote a common understanding of biopsychosocial treatment. Separately, therapists will also receive information about the treatment protocols. To encourage collaboration in the local networks, three additional peer-review meetings of one hour (every 6–8 weeks) are organized by the project team in each local network after the wash-out period. During these meetings, healthcare professionals apply the theories and treatment protocols learned during the education program in daily practice, with room for extra education by the teachers if necessary. After these three peer-review meetings, the local networks are encouraged to organize further such meetings in order to align the working procedures and treatment plans of the patients.

### Control

All networks start with a control period, in which local networks will invite patients who are attending consultations for CMP complaints to participate in the study. The healthcare professionals will refer and treat the patients, following the usual way of working in pain rehabilitation care in the Netherlands. In usual care, patients can receive treatments from a variety of approaches: from a more biomedical to a psychological or biopsychosocial approach. This results in a wide range of treatments that can vary in duration, content, and intensity, like medication prescription, a few sessions of physiotherapy in primary care or a complex multidisciplinary treatment in tertiary care. In usual care, the goal of the treatment does not have to be on daily functioning of the patient.

### Recruitment of primary healthcare professionals

Primary healthcare professionals (therapists, GPs and mental health nurses) working in the Parkstad region (Limburg, the Netherlands) who have no prior experience with NPRL1.0 will be recruited for participation in the study. Social media and the network of healthcare professionals of NPRL1.0 will be used to recruit new healthcare professionals. Healthcare professionals must be willing to recruit patients for the control and intervention periods, to attend the education days, and to make use of the assessment tool and treatment protocol of NPRL2.0.

### Recruitment of patients

Patients with CMP complaints, who visit the participating GPs and therapists via direct access, will be informed about the study and asked for consent to transfer their contact details to the research team. The research team will contact these patients by phone to inform them about the study and ask for oral consent for participation. Subsequently, the patients will receive the first questionnaire (T1) electronically or by post, in which they can give electronic/written informed consent for participation in the study.

Patients will be eligible if they are ≥ 18 years at the start of the study, have CMP or musculoskeletal pain with a high risk of becoming chronic, are willing to improve their functioning despite the pain, and have adequate Dutch literacy to complete the questionnaires. Exclusion criteria are pregnancy or any medical (orthopedic, rheumatic or neurological) or psychiatric disease which could be treated by a more appropriate therapy, according to the expert opinion of the GP. The data will be handled based on intention-to-treat.

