**Methods:**

In this pragmatic study, it is expected that two local networks with 105 patients will participate in the prospective cohort study and six local networks with 184 patients in the stepped-wedge based design. Healthcare professionals in the local networks will recruit patients. Inclusion criteria: age ≥ 18 years; having CMP; willing to improve functioning despite pain; and adequate Dutch literacy. Exclusion criteria: pregnancy; and having a treatable medical or psychiatric disease. Patients will complete questionnaires at baseline (T1), 3 months (T2), 6 months (T3), and 9 months (T4). Questionnaires at T1 and T4 will include the Pain Disability Index and Short Form Health Survey. Questionnaires at T1, T2, T3, and T4 will include the EQ-5D-5L, and iMTA Medical Consumption and Productivity Cost Questionnaires. Outcomes will be compared using linear mixed-model analysis and costs will be compared using bootstrapping methods.

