## Methods

### Study design

In this pragmatic study, the recruiting period will be from April 2019 till March 2020, with follow-ups till December 2020. This study comprises two designs; a prospective cohort study and a stepped-wedge based design.

Two local networks of NPRL1.0 will be enrolled in NPRL2.0. They will receive additional education and information based on the results of the feasibility study of NPRL1.0. In NPRL2.0, they will invite patients to participate in a prospective cohort study.

In the stepped-wedge based design working according to NPRL2.0 will be introduced in three steps in two local primary care networks at the same step (step A, B or C). Local networks that intensively collaborate, due to their geographical location, will be placed together in one step (A, B or C). An independent research assistant will randomly allocate the local networks over the steps. In one local network, at least one therapist, general practitioner (GP), and mental health nurse will participate. Each local network will first recruit patients as controls during a period of care as usual, followed by a 3-month ‘wash-out’ period in which education is given (see Fig. 1). After the wash-out period, a local network will then recruit patients during the intervention period in which NPRL2.0 is the standard of care. According to the stepped-wedge based design, length of control and intervention periods vary in each group: Group A will spend 3 months as control and 5 months with intervention; for Group B, there will be 4 months as control and 4 months with intervention; and Group C will spend 5 months as control and 3 months with intervention. Thus, healthcare professionals in all local networks will recruit patients for participation in both control and intervention groups. Patients will contribute data to either the control group or the intervention group, but not both. A stepped-wedge based design is the most feasible design in this pragmatic study as it has the following advantages: (1) it controls for between-local network variation in daily practice; (2) it gives the opportunity to assess intervention effects in a pre/post comparison across local networks, which increases statistical power; (3) it gives an opportunity to assess learning effects by comparing the results of local networks that transit earlier with those that transit later [34].

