### Outcome measures

#### Baseline characteristics

Baseline characteristics will be collected at T1 and they will include questions about: birth date, gender, nationality, marital status, family composition, level of education, and co-morbidities.

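### The same professionals recruit controls before, and intervention patients after, training in recognising at-risk pain; the at-risk criterion has no threshold and pain duration is not a listed baseline item, so chronicity may differ between groups in an unknown direction

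*Protocol article*

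**What the plan says.** All places are in the protocol article.

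- **Who recruits.** Study design: "Thus, healthcare professionals in all local networks will recruit patients for participation in both control and intervention groups". Each patient belongs to one group only.
- **What changes in between.** Education and collaboration: "Healthcare professionals will receive education during the 3-month wash-out period". The topics include "recognition of patients with or at risk of CMP, providing education to patients with CMP, use of the assessment tool".
- **Who may enter.** Recruitment of patients admits people who "have CMP or musculoskeletal pain with a high risk of becoming chronic, are willing to improve their functioning despite the pain". It gives no duration limit and no risk cut-off.
- **Narrower wording elsewhere.** The abstract has "Inclusion criteria: age ≥ 18 years; having CMP; willing to improve functioning despite pain; and adequate Dutch literacy". For the control period, the Control section says that "local networks will invite patients who are attending consultations for CMP complaints to participate in the study". Neither mentions the at-risk group.
- **What is recorded.** Baseline characteristics lists "birth date, gender, nationality, marital status, family composition, level of education, and co-morbidities". Data collection describes the complexity tool as a pain VAS plus nine yes/no biopsychosocial questions. Controls complete it within the T1 questionnaire, intervention patients in the consultation.
- **How imbalance is handled.** Under Data analysis, a variable enters the model if it is known to relate to the outcome and differs between groups at T1 with p ≤ 0.10.
- **Why balance is expected.** The Discussion expects comparable complexity in the two groups because patients are recruited at their first consultation.

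**The concern.** Randomising networks to steps settles when each network crosses over. It does not settle which patients a professional puts forward before and after crossing. That choice rests partly on judging the risk of chronicity, and the training is meant to change this very judgement. The willingness criterion is open to the same drift: NPRL2.0 aims at functioning despite pain, whereas the Control section says usual care need not aim at daily functioning.

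If the share of not-yet-chronic patients differs between periods and their course differs from that of established CMP, part of the group difference in PDI, EQ-5D-5L and costs reflects selection and not NPRL2.0. The Discussion expects no short-term benefit and hypothesises outcomes no worse than usual care, so even a modest bias could affect the reading. If recognition keeps sharpening with experience, drift in case mix could also be mistaken for the learning effect.

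**Working it through.** The plan gives no figure for this bias, so there is nothing to reproduce. The check compares the sections and then sizes the problem under stated assumptions.

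**1. Does anything hold the selection threshold constant?** Recruitment at the first consultation fixes the timing of selection. It does not fix the judgement that the professional applies, and the Discussion's expectation concerns complexity, not chronicity. The research team phones every patient, but the article describes that call as giving information and obtaining oral consent, not as checking eligibility. In the intervention period the tool is completed in the consultation, so its result could be known when a patient is put forward. In the control period it comes with the T1 questionnaire, after the invitation and the call.

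**2. Would a shift be seen?** A shift in severity or psychosocial complexity would be: T1 includes PDI, SF-12, EQ-5D-5L, pain NRS and the complexity tool. A shift in chronicity might not be: none of the seven listed baseline items is pain duration, and the tool is not described as recording it.

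**3. Would the adjustment rule catch it?** Suppose duration were recorded. The chance that a two-sided comparison of proportions at the 0.10 level, with the planned 92 per group, flags an imbalance is:

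| At-risk share (assumed) | Chance of p ≤ 0.10 |
|---|---|
| 10% v 20% | about 60% |
| 20% v 30% | about 47% |
| 20% v 40% | about 91% |

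For 20% v 30%: the null standard error is √(2 × 0.25 × 0.75 / 92) = 0.0638, so the critical difference is 1.645 × 0.0638 = 0.105. The alternative standard error is √((0.16 + 0.21) / 92) = 0.0634. Then z = (0.100 − 0.105) / 0.0634 ≈ −0.08, a probability of about 0.47. A 10-point imbalance from that base would be missed about half the time.

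**4. How large could the bias be?** Bias in PDI change = (difference in at-risk share) × (difference in mean PDI change between at-risk and established-CMP patients). Both inputs are assumptions; only the 13-point minimal important change comes from the article (Health assessment).

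- Low: 0.10 × 5 = 0.5 points; 0.5 / 13 = 4%.
- Middle: 0.20 × 10 = 2.0 points; 2.0 / 13 = 15%.
- High: 0.30 × 15 = 4.5 points; 4.5 / 13 = 35%.

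The sign depends on which group has more at-risk patients and on which kind of patient improves more. The documents settle neither, so the range is ±0.5 to ±4.5 points.

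**The case against.** The strongest reply concerns direction. A reader might infer that training lets more self-limiting pain into the intervention group and so favours NPRL2.0. The documents do not support that. The criterion is a high risk of becoming chronic, which describes a poor outlook. Better recognition could keep self-resolving cases out, or bring in more complex patients, and untrained professionals could admit low-risk pain in the control period. The Background reports low quality of life and high absenteeism already at 3 to 6 months' duration. Nothing in the article says that recent-onset pain improves more. This part of the reply stands, so the direction is unknown.

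A reader might also infer that no planned variable can deal with the problem. That goes too far. Both groups complete the complexity tool and the other T1 questionnaires, and these can enter the model; health care use and productivity loss may be partial proxies for chronicity. What remains is that the tool is completed in different settings, that none of these measures is described as recording duration, and that entry depends on the p-value.

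Third, the article is condensed, and the figure that sets out the data collection is not shown. Duration may be collected; the point is only that it is not among the listed items. The abstract's shorter wording is likewise ordinary condensation. It matters mainly because the Control section has the same narrow wording.

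Finally, one might want established CMP as the primary comparison. That would remove patients whom the study includes deliberately and would shrink the sample. The article does not call for it.

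**Conclusion.** The point holds as a risk of bias of unknown direction. The textual elements are firm: the same recruiters in both periods, training on at-risk recognition in between, an entry route without a threshold, and no duration among the listed baseline items. The size is illustrative, 0.5 to 4.5 PDI points either way (4% to 35% of the minimal important change), and rests wholly on assumed share differences of 10 to 30 percentage points and prognosis differences of 5 to 15 points. The article supports neither a claim that the result will favour NPRL2.0 nor a claim that the imbalance could not be detected or adjusted for at all. The change is worth making because it is cheap and the plan's one argument for balance does not address the mechanism.

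**What to change.** 1. Record the duration of the current pain at T1 in both groups, if this is not already done. Always include it in the model, with the baseline complexity score, whatever the p-value.
2. Have the research team apply one fixed script for the CMP/at-risk and willingness criteria, in the phone call it already makes, identically in both periods. Align the abstract and the Control section with Recruitment of patients.
3. Report the at-risk share by period, and analyse established-CMP patients alone as a sensitivity analysis, not as the primary comparison.

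The cost is one questionnaire item and a slightly longer call. The script cannot recover patients whom a professional never put forward, which is why the share by period must also be reported. Recruitment was planned to end in March 2020 and the article is dated October 2020. If it has closed, the script is no longer possible; duration would have to come from data already collected or from patient records, while covariate adjustment and reporting remain open.

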### Sample size

In the prospective cohort, all patients with CMP who visit the two local networks of NPRL1.0 will be invited to participate in the study. Based on the recruitment results of the feasibility study of NPRL1.0, and the number of patients visiting a GP practice, we expect that each local network will also recruit about six patients per month. Therefore, the two local networks from NPRL1.0 together should recruit approximately 132 patients in 11 months. Assuming a dropout rate of 20%, we expect to include approximately 105 patients in this study.

To calculate the desired sample size for the stepped-wedge based design, we used the method described by Woertman et al. [39]. The calculations of the number of patients needed are based on the primary outcome of the cost-utility analysis, the health-related quality of life measured with the 5-level EQ-5D version (EQ-5D-5L). Based on McClure et al., we consider an increase of 0.063 points (SD = 0.013) in 1 year as clinically relevant [40]. In addition, an alpha of 0.05, a power of 80%, a 1:1 ratio between control and intervention groups, and a dropout rate of 30% were assumed. Based on these values and the stepped-wedge based design, a design effect (DEsw) of 0.416 exists, which leads to a required sample size of 184 patients (92 control and 92 intervention). Based on the recruitment results of the feasibility study of NPRL1.0, and the number of patients visiting a GP practice, we expect that each local network will recruit 6 patients per month [32]. Therefore, with a dropout rate of 30% of local networks, six local networks will need to participate.

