The EQ-5D-5L will be used for the cost-utility analysis: it provides a single health index based on self-reported mobility, self-care, usual activities, pain/discomfort, and anxiety/depression, with a minimal clinically important change of 0.04 [47]. There are five levels in each dimension from which respondents select that which most closely matches their health state. The levels are no, slight, moderate, severe, and extreme problems, coded 1 to 5. A health state index score, ranging from − 0.446 to 1 (worst to best imaginable health status), will be calculated from individual health profiles, using the Dutch utility tariff [48]. QALYs were calculated from utilities by using the area under the curve method. The accompanying visual analogue scale (VAS: 0–100) rates the current health state, with higher scores indicative of better experienced health. The minimal clinically important difference for low back pain is 22.5 [46]. The Dutch version of the EQ-5D-5L was found valid and reliable [49, 50].

The Numeric Rating Scale (NRS) will be used to measure pain intensity on an 11-point scale varying from 0 (no pain) to 10 (worst pain imaginable). At each measurement point (T1-4), the patient will complete the NRS three times: current pain intensity; lowest pain intensity in the last week; highest pain intensity in the last week. The NRS has shown high test–retest reliability and validity [51]. A reduction of 2 points, or 30%, on the pain NRS scores can be seen as clinically important [52].

The Hospital Anxiety and Depression Scale (HADS) consists of 14 items of which seven are related to anxiety and seven to depression. The patient is asked to rate the items on a 4-point scale ranging from 0 (not at all) to 3 (most of the time). Total scores range from 0 to 21 on each subscale: a higher score reflects higher distress. The HADS has a sensitivity and specificity of about 80% and a predictive validity for identification of about 70% [53]. The reliability ranges from 0.84 to 0.96 [54].

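### The inputs printed for the EQ-5D-5L sample size (difference 0.063, SD 0.013) give about 1 patient per arm, not 92, so the stated 80% power cannot be verified

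*Protocol article*

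**What the plan says.** All inputs are in the protocol article, under Sample size. The outcome is "the health-related quality of life measured with the 5-level EQ-5D version (EQ-5D-5L"). The difference and the only EQ-5D-5L SD in the article come together: "we consider an increase of 0.063 points (SD = 0.013) in 1 year as clinically relevant". The other assumptions are "an alpha of 0.05, a power of 80%, a 1:1 ratio between control and intervention groups", and "a dropout rate of 30% were assumed". The article then says that these values, with the stepped-wedge structure, yield "a design effect (DEsw) of 0.416 exists, which leads to a required sample size of 184 patients (92 control and 92 intervention").

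Two other places bear on this. The Health assessment section gives the index range as -0.446 to 1 and describes the instrument "with a minimal clinically important change of 0.04". The Data collection section puts the last questionnaire, T4, at 9 months after T1.

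**The concern.** The section links its inputs to its output explicitly, so a reader should be able to get from one to the other. With the printed SD that is impossible by two orders of magnitude. This is the article's only power calculation; the cohort part has an expected number of patients but no power statement. If the SD behind it is unknown, nobody can judge what a null result on the EQ-5D-5L would mean, because the power of 184 patients depends strongly on that SD.

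**Working it through.** **Inputs** (Sample size section unless noted): difference 0.063; SD 0.013; alpha 0.05, taken as two-sided because sidedness is not stated; power 80%; ratio 1:1; dropout 30%; design effect 0.416, taken as stated; index range -0.446 to 1 and minimal important change 0.04 (Health assessment).

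**1. Attempt to reproduce 184.**

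n per arm = 2 × (1.960 + 0.842)² × (SD/difference)² = 15.70 × (0.013/0.063)² = 0.67.

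Total = 2 × 0.67 = 1.34. Times 0.416 = 0.56. Divided by 0.70 = 0.79. The plan states 184.

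Variants that keep 0.013 as an SD do not help. One-sided alpha gives 0.53 per arm. The exact t-test gives 3 per arm, or 5 per arm after 30% dropout without the design effect. That total of 10 is the largest any such variant reached. With 92 per arm and SD 0.013, power would be essentially 100%.

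**2. Could 0.013 be a between-patient SD?** The index is 1.446 wide, and 0.013/1.446 = 0.9% of it. The article's own minimal important change would be 0.04/0.013 = 3.1 SDs, and the target difference 0.063/0.013 = 4.85 SDs. That is not credible for patients with chronic pain. It is an inference, but one from the article's own figures.

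**3. Could it be a simple slip?**
- Misprint for 0.13: 80 patients with the design effect, 192 without it (196 by t-test).
- A variance, so SD = √0.013 = 0.114: 62 with the design effect, 149 without it.

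None of these gives 184.

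**4. Which SD would give 184?** If 184 includes 30% dropout and the design effect applies: 184 × 0.70 / 0.416 / 2 = 154.8 per arm, so SD = 0.063 × √(154.8/15.70) = 0.198. If 184 contains no dropout allowance: 184 / 0.416 / 2 = 221 per arm, so SD = 0.237.

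**5. What is at stake.** Keep the difference at 0.063, the design effect at 0.416 and 30% dropout within the 184. Power = Φ(0.063/SD × √(154.8/2) − 1.960), and required total = 2 × 15.70 × (SD/0.063)² × 0.416 / 0.70. The SDs are assumed values; the article gives none that could serve.

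| Assumed SD | Power of 184 | Total needed for 80% |
|---|---|---|
| 0.15 | 96% | about 106 |
| 0.20 | 79% | about 188 |
| 0.25 | 60% | about 294 |
| 0.30 | 46% | about 423 |

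**The case against.** The best defence is that the calculation may be sound and only its report faulty. The article attaches 0.013 to the clinically relevant increase and never calls it the spread between patients, so it may be a mislabelled figure beside an unreported working SD. An SD near 0.198 does yield 184 with the stated design effect and dropout. Other routes that the article does not describe also arrive there. A standardised effect of 0.5 needs 64 per arm by t-test, and 64/0.70 rounds up to 92 with no design effect. Reading 0.013 as a variance and multiplying by three gives 102.8 × 0.416 / 0.70 × 3 = 183.3, or 92 per arm after rounding up. This stands: 184 may have come from a reasonable calculation. But these routes imply different SDs (0.198, 0.126, 0.114), so the article does not identify which was used, and under each of them the printed SD is still wrong or wrongly labelled.

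Three stronger readings are tempting and not supported.
- *The trial is too small.* Nothing shows this. Planned recruitment of 6 networks × 8 months × 6 patients per month = 288, or about 202 after 30% loss, exceeds 184. That speaks to feasibility, though, and does not validate the power.
- *Power is only 43% at the article's own threshold of 0.04.* That figure presupposes exactly 80% power at 0.063, which is the claim that cannot be verified.
- *0.063 and 0.04 contradict each other.* They cite different sources, and a trial may be sized for more than a minimal change. The choice deserves a sentence of explanation, but it is not a proven inconsistency.

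**Conclusion.** The point holds in this form: the step from the printed inputs to 184 patients is wrong as written, and the 80% power cannot be checked. The gap is 0.67 against 92 patients per arm, and no reading that keeps 0.013 as an SD narrows it materially. This rests on a standard two-group comparison of means and on the design effect as stated. That 0.013 is not a between-patient SD is a strong inference, not something the article says. Whether true power is above or below 80% is open: over an assumed SD range of 0.15 to 0.30 it runs from about 96% to 46%. The reference to 1 year, when measurement ends at 9 months, is a real but minor mismatch.

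**What to change.** In the Sample size section:
- Replace the printed SD by the between-patient SD actually used, with its source. It should not be a value back-solved to fit 184.
- Restate the power of 184 patients with that SD, and add a sensitivity range such as the table above, labelled as assumed.
- State whether alpha is two-sided and whether 184 is before or after dropout.
- Align the 1-year wording with the 9-month follow-up.
- Say in one sentence why 0.063, rather than the 0.04 given under Health assessment, is the target difference.

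The cost is one rewritten paragraph, with no extra enrolment and no design change. The downside is that the restated power may be less favourable than 80%.
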